**Table 5. Health Utilization Outcomes**

| Condition                      | Description                                                                                                               | How outcome will be identified                                                                                |
|--------------------------------|---------------------------------------------------------------------------------------------------------------------------|---------------------------------------------------------------------------------------------------------------|
| ED return visits within 7 days | Within 7 days of index ED visit, did the patient have another ED visit to the same institution or a different institution | 
 
1. Billing records
 
2. EHR
 
3. Chart review
 
 |
| Disposition                    | Plan following index ED visit                                                                                             | 
 
1. Discharge home
 
2. Admitted to inpatient unit
 
    |
| ICU admission                  | Hospitalization in an intensive care unit (ICU)                                                                           | 
 
1. CPT codes
 
2. Chart review
 
                       |

|                         |                                                                                                     |                                                  |
|-------------------------|-----------------------------------------------------------------------------------------------------|--------------------------------------------------|
| ED length of stay       | Time from initial triage to disposition, for index ED visit.                                        | Time stamps from EHR data                        |
| Hospital length of stay | Number of consecutive days in an inpatient setting (includes short stay, observation unit and ICU). | 1. Billing records
2. Chart review to confirm |

**Table 6. Missed Care for Other Abdominal Emergencies**

| Condition                                      | Description                                                                                        | How outcome will be identified                                                                                                                                                                                                      |
|------------------------------------------------|----------------------------------------------------------------------------------------------------|-------------------------------------------------------------------------------------------------------------------------------------------------------------------------------------------------------------------------------------|
| Medical emergencies that require intervention  | Small bowel obstruction, tub-ovarian abscess, pelvic inflammatory disease, pyelonephritis          | 1. Diagnoses within 7 days of index ED visit will be identified from EHR and billing records via ICD-10 codes
2. Potential cases will be manually reviewed by site PIs to determine whether there was a delay in definitive care |
| Surgical emergencies that require intervention | ovarian torsion; testicular torsion, abdominal tumor, intussusception, volvulus, ectopic pregnancy | 1. Diagnoses within 7 days of index ED visit will be identified from EHR and billing records via ICD-10 codes
2. Potential cases will be manually reviewed by site PIs to determine whether there was a delay in definitive care |

Safety outcome rates for intervention and control EDs will be reported to the IDMC every 6 months throughout the 2 year cluster randomized trial. Eligibility and enrollment will also be tracked and reported to the IDMC every 6 months, starting in the pre-intervention period. An example of the enrollment table is shown below (Table 7).

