### Identification of a cohort of patients with acute abdominal pain at risk for appendicitis (Hypothesis 1):

Using existing EHR data and simple prompts implemented at triage at all 17 sites over the 6-month pre-intervention period and 24-month trial we will identify our study cohort of children and adolescents at elevated risk for appendicitis. The algorithm underlying this tool will exclude patients with chronic abdominal pain, abdominal trauma, and/or pregnancy, because their management is beyond the scope of the proposed intervention. For patients undergoing an appendectomy within 7 days of their index ED visit, a trained, blinded nurse abstractor will review their pathology report. For patients undergoing appendectomy, appendicitis is defined by specific terminology on the pathology report, as in our previous multicenter study (consistent with appendicitis, neutrophil invasion of tissue, serosal inflammation, acute peri-appendicitis, or acute appendicitis). For patients with perforation undergoing drainage and/or intravenous antibiotics and interval appendectomy, diagnosis will be based on clinical notes from the treating surgeon. For patients transferred from the ED where they initially sought care to a facility with pediatric surgical expertise, we will seek final diagnoses and pathology reports from the receiving institution. If we are unable to verify final diagnosis, the patient will be excluded from primary analyses. These patients may be included sensitivity analyses with the diagnosis of appendicitis or not appendicitis assigned based on provider impression and imaging available at the time of ED discharge / transfer. For HPMG, outside of the study EDs, Children's Hospital would be the primary outside institution to receive transfers for further evaluation and appendectomy. Thus, we will establish a registry of patients with a discharge diagnosis of appendicitis from Children's Hospital and use a probabilistic method to determine whether these patients are matches with patients receiving care in the HPMG study EDs. KPNC uses a hub and spoke system for pediatric surgery. Among the 11 CREST sites are four pediatric surgical hubs.

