### Monitoring Procedures

A passive surveillance strategy is proposed to monitor adverse events in the study population. Programs will be automated to collect appropriate safety variables and data analyzed by KP and HP programmers/analysts and the study statistician, [name]. Clinical records for all potential adverse events will be reviewed by one or more investigators at that site. Reports will be presented at biannual meetings and summaries of IDMC recommendations will be submitted to participating IRBs.

Study data are accessible at all times for the PI and co-investigators to review. During the intervention

period, the PI and co-investigators will monitor study conduct (subject accrual, CDS use rates) on a bi-weekly basis. The PIs, co-investigators, and IDMC will safety data in aggregate on a bi-annual basis. The PIs will ensure that all protocol deviations, AEs, and SAEs are reported to the NICHD and IRB according to the applicable regulatory requirements.

This is a minimal risk study that proposes a passive safety surveillance strategy. To evaluate potential adverse events, we will collect and report on automated data for patients with a chief complaint of abdominal pain at intervention and control ED sites. Specific safety outcomes to be evaluated will be reviewed and approved by the IDMC. Proposed safety outcomes are listed in Tables 4-7 below.

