**Labs**

**WBC results:**  k/ul | WBC Measured Date: 08-17-2017

**ANC results:**  k/ul | ANC Measured Date: 08-17-2017

Go Back

Calculate Appendicitis Risk

Once all questions are answered, click "Calculate Appendicitis Risk".

[figure not shown]

The summary and management suggestions can be copied into the provider note in the EHR. If lab data is not available for data extraction at the time the user accesses the CDS, the option to enter a theoretical WBC and ANC is available and a pARC score will be calculated based on the theoretical value. In some cases, there may be no data transferred from the EHR. In these instances, the user is able to enter data directly into the full CDS and calculate a pARC score.

To account for differences in workflow and the possibility that a provider may order imaging up front before utilizing the full CDS tool, there is an alert that displays when abdominal imaging is ordered. The imaging alert also includes a link to the full CDS and suggests to the user that using the pARC score is recommended before imaging. A screenshot of the imaging BPA is shown below.

Imaging alert for CDS prompting user for additional information.

\*\*\* Patient with acute abdominal pain \*\*\*

If you are ordering a CT or US to evaluate for appendicitis, APPY CDS may be useful.

A CBC with differential is used in the appendicitis risk calculator.

Once the CBC with diff results are available and before placing an imaging order, click [HERE](#) to calculate patient's appendicitis risk using APPY CDS.

[Information on pARC score](#)

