**PATIENT SUMMARY**

[name] presented to the ED with RLQ pain, nausea and vomiting. His exam reveals no RLQ tenderness and his WBC & PMN are normal range. His pARC score is XX % and he is XX risk. He will be discharged home.

BACK COPY & SUBMIT SUBMIT

Similar to the design at HealthPartners, RISTRA has mechanisms in place for when the CBC has not been completed and results are not back. In these cases, the provider will see a form that gives them an option to refresh RISTRA once the results are indicated in the EHR before they continue the CDS. The clinician also has the option to use a sliding scale to visualize what the pARC score might be using theoretical WBC values (see below). Once the CBC has resulted and the provider refreshes the RISTRA form, the provider can continue with the CDS to get the actual calculated risk of appendicitis.

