## Appendix D: Data Collection Instruments

### Appendicitis Chart Review Form for final outcomes- HealthPartners.

Appy CDS Chart Review  
Page 1 of 3

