#### Imported Information

MRN \_\_\_\_\_  
DOB : [dob]  
Date of Index Emergency Department visit : [index\_er\_date]  
Date of Index date + 7 days (pre-populated in Excel) : [index\_7days]  
Gender : [gender]  
Site for index ED visit  
☐ Regions  
☐ Lakeview  
☐ Westfield  
☐ Hudson  
☐ Methodist  
☐ Amery

---

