#### Imported Information

Date of Index Emergency Department visit : [index\_er\_date]

Date of Index date + 7 days (pre-populated in Excel) : [index\_7days]

Gender : [gender]

HealthPartner's date of discharge

\_\_\_\_\_  
(MDY)

Which HP hospital was patient at?

- ☐ Regions
- ☐ Lakeview
- ☐ Westfield
- ☐ Hudson
- ☐ Methodist
- ☐ Amery

Was patient transferred to Children's?

- ☐ Yes
- ☐ No  
(Came to Children's from HP facility within 1 day)

Date and time of Children's ED visit

\_\_\_\_\_  
(MDY H:M)

How did the patient arrive at Children's ED?

- ☐ Car
- ☐ EMS
- ☐ Public Transportation
- ☐ Other

If other, how did the patient arrive?

\_\_\_\_\_

Did the patient have surgery during this visit?

- ☐ Yes
- ☐ No

What date and time was the operation?

\_\_\_\_\_  
(MDY H:M)

Did the patient have surgery for appendicitis during this visit?

- ☐ Yes
- ☐ No

What date and time was the surgery for appendicitis performed?

\_\_\_\_\_  
(MDY H:M)

Was this a negative appendectomy?

- ☐ Yes
- ☐ No

(from the pathology report)

(Key Words for Negative Appendectomy: No evidence for neutrophil invasion of tissue, lymphoid hyperplasia present with no evidence for appendicitis, no serosal injection present)

What does pathology report indicate?

\_\_\_\_\_

Final Diagnosis for this visit

- ☐ Appendicitis
  - ☐ Perforated Appendicitis (from operative note)
  - ☐ Medical Diagnosis
  - ☐ Other Surgical
- (Perforation Key Words: Ruptured appendix, abscess noted in the right lower quadrant, purulent material in abdomen, likely perforated appendicitis, or "complex appendicitis")

What did the operative note indicate?

(Perforation Key Words: Ruptured appendix, abscess noted in the right lower quadrant, purulent material in abdomen, likely perforated appendicitis, or "complex appendicitis")

Which medical diagnosis

- ☐ Non-specific abdominal Pain
- ☐ Constipation
- ☐ Gastritis
- ☐ Gastroenteritis
- ☐ Mesenteric Adenitis
- ☐ PID
- ☐ Renal Stone
- ☐ UTI
- ☐ Other Medical Diagnosis

Did the patient have any of the following surgical emergencies during this visit?

- ☐ Ovarian torsion
  - ☐ Testicular torsion
  - ☐ Abdominal tumor
  - ☐ Intussusception
  - ☐ Volvulus
  - ☐ Ectopic pregnancy
  - ☐ N/A
- (Check all that apply)

Did the patient receive imaging at Children's during this visit?

- ☐ Yes
- ☐ No

What imaging studies did the child receive?

- ☐ Xray
- ☐ Ultrasound
- ☐ CT
- ☐ MRI

Did any of the following medical emergencies occur during this visit?

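### Delayed care is judged by site PIs who know the allocation and have no stated criteria, and the one stated blind (pathology review) is not protected by the HP and Children's forms

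*Combined protocol and SAP*

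**What the plan says.** Three sets of statements bear on who reviews outcomes and what they know.

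- **Stated blinding.** Section 6b, in the paragraph on identifying the Hypothesis 1 cohort, says that for patients having an appendectomy within 7 days "a trained, blinded nurse abstractor will review their pathology report". It does not say what the abstractor is blinded to or how. No blinding is stated for the safety outcomes in section 6b or in Tables 4 to 6.
- **Forms.** Appendix D gives the "Appendicitis Chart Review Form for final outcomes- HealthPartners", which has an abstractor ID and an item for pathology findings. Its imported fields include "Site for index ED visit", with the six HealthPartners EDs listed, and later items list hospitals again for disposition and for the place of surgery. The Children's Minnesota form asks "Which HP hospital was patient at" and also records negative appendectomy and perforation.
- **Safety review.** Table 6 covers medical and surgical emergencies other than appendicitis. Candidates are found by ICD-10 code, and then: "Potential cases will be manually reviewed by site PIs to determine whether there was a delay in definitive care". Under Monitoring Procedures: "Clinical records for all potential adverse events will be reviewed by one or more investigators at that site".

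On CDS text in the chart, Appendix A says "The summary and management suggestions can be copied into the provider note in the EHR", and the Kaiser summary template in Appendix B contains "His pARC score is XX % and he is XX risk".

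**The concern.** Whether definitive care was delayed is the most discretionary judgement among the safety outcomes. It is also the place where the plan looks for harm that less CT might cause in conditions other than appendicitis. It is assigned to people who run the intervention and know which EDs have it. If they read candidate cases more leniently, or more strictly, in one arm, the comparison shifts before the six-monthly rates reach the IDMC. The IDMC may choose to stay masked, but that cannot correct classifications already made. The Dissemination section leans on the safety outcomes to reassure clinicians who hesitate to discharge a child without a negative CT, so this result will be used.

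The pathology review is a smaller matter. There the plan promises a blind, and its own forms show the information most likely to break it.

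**Working it through.** The plan states no figure on this point, so there is none to reproduce. The first three steps set the texts side by side; the fourth is an illustration.

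**1. Does the form reveal the arm?** EDs are the randomised units, and section 4 says assignment is disclosed before implementation. The two forms name the ED but carry no arm field. An abstractor who knows the allocation therefore learns the arm from the form. No redaction or separate site field is described. The HealthPartners form also carries the record number, so the abstractor can open the whole chart.

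**2. Do the Table 6 reviewers know the arm?** Section 5c has site PIs train the Champions and provide the CDS-use reports passed to clinicians at intervention EDs. Monitoring Procedures gives the PI and co-investigators access to study data at all times. Knowledge of allocation follows from the role.

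**3. How much judgement does each safety outcome leave?**
- Perforation: mainly key terms in the operative note. Limited.
- Negative appendectomy: pathology report. Limited.
- Missed appendicitis: code search, then a 7-day date check. Limited.
- Delayed care (Table 6): code search, then a reviewer's opinion with no criteria and no second reader. Wide.

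**4. How sensitive is a count this small?** Inputs:
- Projected two-year enrolment in Table 7 (an example table): intervention I = 684 + 2,536 = 3,220; control = 528 + 1,920 = 2,448.
- Candidate rate r: assumed 1.1%, range 0.5% to 2%. The 1.1% is the frequency of surgical conditions other than appendicitis in the earlier multicenter study cited in section 2b. That is a different cohort, and Table 6 also counts medical emergencies.
- Proportion of candidates truly delayed, d, equal in both arms: assumed 20%, range 10% to 30%.
- k intervention cases called not delayed because of knowledge of arm.

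The true ratio is 1.00. The observed ratio is [(I·r·d − k)/I] / (r·d) = 1 − k/(I·r·d).

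At r = 1.1% and d = 20%, there are 35.4 and 26.9 candidates. Delayed cases are 3,220 × 0.011 × 0.20 = 7.1 and 2,448 × 0.011 × 0.20 = 5.4. With k = 2, the ratio is 1 − 2/7.08 = 0.72.

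| r | d | Delayed, intervention v control | Ratio at k = 1, 2, 3 |
|---|---|---|---|
| 0.5% | 20% | 3.2 v 2.4 | 0.69, 0.38, 0.07 |
| 1.1% | 10% | 3.5 v 2.7 | 0.72, 0.44, 0.15 |
| 1.1% | 20% | 7.1 v 5.4 | 0.86, 0.72, 0.58 |
| 1.1% | 30% | 10.6 v 8.1 | 0.91, 0.81, 0.72 |
| 2% | 20% | 12.9 v 9.8 | 0.92, 0.84, 0.77 |

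This shows fragility, not an expected bias. Stricter calls at intervention EDs would move the ratio the other way.

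**The case against.** Several stronger readings are tempting, and the documents do not support them.

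- *A general safety-outcome blind fails.* There is none to fail. Blinding is stated only for the pathology review; for Table 6 it was never planned.
- *The arm is known for every HealthPartners case.* The forms name an ED, and no text says that the HealthPartners or Children's abstractors know the allocation. The forms create a risk, not a certainty. No Kaiser abstraction form is shown, and Kaiser accounts for 11 of 17 EDs and 2,536 + 1,920 = 4,456 of 5,668 projected patients (79%).
- *Pasted CDS text unblinds the pathology review.* Copying is optional, since the Kaiser screen also offers a submit button without copying. The text goes into the provider note, not the pathology or operative report. It matters only to a reviewer who reads ED notes, as one judging delay probably would.
- *All the safety outcomes turn on judgement.* Perforation and missed appendicitis rest mainly on key terms, codes and a date check.
- *Dismissing a quarter of intervention cases would hide a one-third increase in harm.* That is true by construction at any event rate (0.75 × 1.33 = 1.00), and the quarter has no source. It measures nothing about this trial.
- *Harm would be hidden from the IDMC.* The IDMC also reviews serious adverse event documentation and receives missed appendicitis cases. Return visits, ICU admission and length of stay come largely from billing, procedure-code or EHR data.
- *Each PI judges only his or her own ED.* The documents sometimes use site for a whole health system, so one PI may review both arms. That PI would still be unmasked.

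The sponsor can fairly add that this is a minimal-risk trial with passive surveillance and that its main outcomes are objective. What remains standing is the unmasked, criterion-free judgement of delay and a pathology blind with nothing to protect it.

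**Conclusion.** The point holds in two parts. The main one is that delay in care is judged by site PIs who know the allocation, with no masking, criteria or second reader. Potential adverse events likewise go to investigators at the same site. This applies to both health systems. The lesser one is that the stated blind for pathology review is not protected by the HealthPartners and Children's forms; for Kaiser this cannot be assessed.

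The size is uncertain because the documents give no rate of delayed cases. Under the assumptions above, two reclassified cases take a true ratio of 1.00 to 0.72 in the central case, and to between 0.38 and 0.84 when the candidate rate runs from 0.5% to 2% with 20% delayed. The conclusion that a few calls could matter rests on the count of delayed cases being small. It does not assert that reviewers will be biased, or in which direction.

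The effectiveness conclusions are not affected: CT and total imaging are taken from completed orders and CPT codes. The change is worth making because the safety reassurance draws on these reviews and the cost is low.

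**What to change.** 1. **Forms.** On the HealthPartners and Children's forms, hide the index-ED field and the hospital lists (disposition and place of surgery) during abstraction, and link them back by study ID afterwards. The Appendix E datasets already hold site alongside study ID, and the listed HealthPartners-to-Children's transfer fields in section 7a do not include the hospital. Give the abstractor extracted pathology and operative text with hospital names removed, not the full chart. Say in section 6b what the abstractor is blinded to.
2. **Delay and adverse-event review.** In Table 6 and Monitoring Procedures, assign each case to an existing investigator from another ED in the same health system, working from an extract with ED name, provider and any pARC or CDS text removed. Such a reviewer still belongs to the study team, so the masking of the extract is what gives protection. Have the investigators write criteria for delay before any arm-level review. Staying within one health system avoids moving chart text between them.
3. **Cases that cannot be masked.** Flag them and report the safety comparison with and without them.

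The cost is a form edit, a redaction step by the existing data team and a reallocation of reviews. No new assessors are needed. The downside is some preparation time for each candidate case.

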**Table 7. Example Enrollment Table**

|                                                      | HP                         |                       | KP                         |                       |
|------------------------------------------------------|----------------------------|-----------------------|----------------------------|-----------------------|
|                                                      | Intervention
2 clusters | Control
2 clusters | Intervention
4 clusters | Control
4 clusters |
| Pre-Intervention period (n)                   | 204                 | 75             | 853                 | 767            |
| Per cluster (n)                               | 102                 | 38             | 213                 | 192            |
| Goal per cluster (n)                                 | 200                        | 200                   | 200                        | 200                   |
| Intervention period (n)                              | 114                        | 88                    | 317                        | 240                   |
| Projected annual                                     | 342                        | 264                   | 1268                       | 960                   |
| Projected over 2-year
intervention period | 684                 | 528            | 2536                | 1920           |
| Projected per cluster (n)                     | 342                 | 264            | 634                 | 480            |
| Goal per cluster                              | 400                 | 400            | 400                 | 400            |

Missed eligibles may occur at several stages. First, the Triage BPA may not fire due to changes in workflow and timing of nurse charting of chief complaint. Second, the Triage BPA may not be completed, thus eligibility cannot be confirmed. Third, patients with final diagnosis unavailable, perhaps due to transfer to an outside facility, cannot be captured.

We will compare ED visits for the target age group with abdominal pain as a chief complaint to confirm either cohort entry or intentional exclusion. Those who appear to be eligible but not included in the cohort will be listed as missed eligible. On a quarterly basis we will review missed eligible cases and review for cases of appendicitis in this group.

